### Process evaluation

We will use the UK Medical Research Council (MRC) process evaluation framework [15] to describe how the intervention works (or does not work) along the pathway of implementation, including the internal dynamics of the four components of the QUALI-DEC strategy. The process evaluation also explores the roles, perceptions, and coping strategies of actors, adaptation of the interventions based on the local context, and any unintended effects, with a view to understand the mediating effect of the context [29]. Figure 3 presents the key functions of the QUALI-DEC process evaluation and the relations among them, while Fig. 4 shows the data collection and analysis methods.

**Fig. 3 Fig3:**
[figure not shown]
Key functions of the process evaluation and the relations among them (adapted from Moore 2015) [15]

**Fig. 4 Fig4:**
[figure not shown]
Data collection and analysis methods for process evaluation

To align the intervention and the implementation strategy to the local context, we conduct qualitative research, document review at the country level, and a readiness assessment of each participating facility. The qualitative research will include semi-structured interviews with women, potential companions, and healthcare providers to obtain a comprehensive understanding of the health system and societal context in each country [19]. Additional interviews with policy-makers and representatives of women’s and professional associations (gynecologists-obstetricians and nurses/midwives) will allow us to complete the stakeholder mapping and analysis. Following the context assessment and in consultation with QUALI-DEC developers and implementers, we will define assumptions on what may need to happen (mechanisms of change), and we will hypothesize about how change will happen at the individual level (healthcare providers, women, and companions), at the organizational level (healthcare facility), and through the interaction of participants. Discussions and meetings will be held by video conference with country researchers and during face-to-face meetings with high-level stakeholders and local OLs in each country. To further assess the potential scalability of the intervention within the countries, we will include a participative scalability assessment in the in-country meetings to summarize early opportunities and challenges for scale up [30].

We will construct a theory of change to guide the process evaluation. We will define indicators of fidelity (whether the intervention was delivered as intended), dose (the quantity of intervention implemented), and reach of intervention (whether women and providers came into contact with each relevant component of QUALI-DEC) [15]. These indicators will be measured at the individual and organizational levels in all facilities using quarterly monitoring visits at each hospital and data from the postpartum cross-sectional survey (proportion of women who used the DAT during antenatal care or chose a companion during labor).

We will conduct in-depth case studies in a subset of four hospitals per country to investigate the details of what worked, why, and why not. Study sites will be purposively selected based on indicators of fidelity, dose, and reach to reflect the diversity of implementation across participating hospitals. Structured observations of each site and on-site meetings will be held with the members of the local committee, maternity ward staff, and facility administrator. In-depth interviews with providers and women will provide more detailed information on the perceptions and views of both stakeholders. The study instrument for IDIs with healthcare providers will be a semistructured interview guide covering the following topics: communication; interprofessional interaction; acceptability of the CS audit and feedback, DAT and labor companionship; and decision-making, including aspects of position/seniority, gender, weighing of alternatives and their implications, and information-sharing. The study instrument for IDIs with women and their companions will be a semistructured interview guide covering the following topics: process of and factors affecting the decision-making to use DAT and labor companionship; perceptions of the DAT and labor companionship related to knowledge, experiences, and support in choosing the mode of childbirth; perceptions and experiences of the relationship between themselves and providers; perception and experiences of how use of the DAT and/or labor companionship influenced trust, self-esteem, empowerment, and the relationship with providers. All interviews will take place in a private setting and will be audio recorded.

### Economic evaluation

The cost-effectiveness of the QUALI-DEC intervention and the financial risk protection provided are important factors for decision-makers considering implementing new strategies to reduce unnecessary CS. We will use an extended cost-effectiveness analysis (ECEA) approach to evaluate the cost-effectiveness of the QUALI-DEC intervention [31]. The impact of QUALI-DEC will be estimated in three domains across women in distinct wealth strata: (i) health gains (e.g., reduced CS rates), (ii) women’s out-of-pocket (OOP) expenditures averted by reducing unnecessary CS, and (iii) total net cost of the intervention to the implementer (see Additional files 1, 2 and 3).

### Sample size

Limited guidance is available on sample size calculation for time series analyses, and many of the recommendations focus on the need for sufficient time points pre- and postintervention to precisely ascertain trends and levels [32, 33]. Our analysis on the primary outcome (monthly CS rates among low-risk women) will include 12 time points preintervention, 24 time points during the intervention phase, and 24 time points during the follow-up phase.

The approach for calculating the required number of participants for the postpartum cross-sectional survey is used for a “before-after” noncontrolled study design. We estimated that a sample of 470 women at baseline and 470 women at the end of the intervention period will ensure 90% statistical power to detect an effect size of 0.3 standard deviations or greater in satisfaction scores with a two-sided 5% significance level [34]. The calculation accounted for the clustered nature of the data by hospitals with a design effect of 2. Allowing for a 20% nonresponse rate, we aim to recruit 564 women in each phase. The proposed sample size (i.e., 564) can be achieved with 2 weeks of data collection in Argentina and Burkina Faso and with 1 week of data collection in Thailand and Vietnam. This sample size will be for each country and will allow to draw conclusions independently for each country and produce individual country interpretations. We estimated that 3980 births will occur during this data collection period in all participating hospitals of the four countries. This overall sample size for the cross-sectional survey will ensure accurate measurements of other secondary outcomes (maternal and perinatal morbidity, time of breastfeeding initiation). Estimations of outcomes at each time point will fluctuate within a 95% confidence interval with the following bounds: 10% rate ± 1% (example: postpartum hemorrhage); 20% rate ± 1.3% (example: second-degree perineal trauma); 40% rate ± 1.5%; (examples: overall CS rate, breastfeeding within 1 h of birth).

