### Targeted sites and participants

The study will be conducted from January 2020 to December 2024, in 32 healthcare facilities (8 per country) with high CS rates. Facilities were selected purposely with country investigators to reflect the range of contexts, such as secondary and tertiary levels of care, public and private hospitals, and teaching and nonacademic facilities (Table 4). The intervention directly targets healthcare providers involved in obstetric care and all women who give birth in the participating hospitals during the study period. We have defined providers as obstetricians and nurses/midwives working in the maternity ward in the study facilities. Women will be eligible if they give birth to a newborn (birthweight ≥ 500 g in Argentina and Vietnam or ≥ 1000 g in Burkina Faso and Thailand), alive or dead, and with or without malformations. The intervention does not target patients admitted for abortion or miscarriage or those who delivered at home or in another facility that is not a participating hospital.

**Table 4 Tab4:** Characteristics of participating hospitals by country

Characteristic	Argentina	Burkina Faso	Thailand	Vietnam
Type of hospital				
Public without private ward	8	8	0	2
Public with private wards	0	0	8	4
Private	0	0	0	2
Level of reference				
Tertiary	4	2	6	2
Secondary	4	4	2	4
Primary	0	2	0	2
Teaching hospital				
Yes	8	3	8	4
No	0	5	0	4
Type of medical records				
Electronic	8	0	4	1
Paper-based	0	8	4	7
Range of annual births	1200-5600	2500-6000	2500-7500	2800-42,000
Range of CS rates	23-38%	21-48%	36-56%	23-54%

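### The survey target of 564 adds 20% to 470 instead of dividing by 0.8; 20% non-response needs 588, a small slip that may not bind

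*Protocol article*

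**What the plan says.** The Sample size section sizes the postpartum survey on satisfaction scores. The number required is given as "a sample of 470 women at baseline and 470 women at the end of the intervention period". The target is 90% power for a difference of 0.3 SD, tested two-sided at 5%. On clustering the section says: "The calculation accounted for the clustered nature of the data by hospitals with a design effect of 2". It then moves from women needed to women sought: "Allowing for a 20% nonresponse rate, we aim to recruit 564 women in each phase". The number applies country by country: "This sample size will be for each country and will allow to draw conclusions independently for each country".

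The same section uses 564 to judge the length of data collection: "The proposed sample size (i.e., 564) can be achieved with 2 weeks of data collection in Argentina and Burkina Faso". For Thailand and Vietnam it allows one week. It expects 3980 births in these windows over the four countries together and gives no breakdown by country. The Outcomes section adds that the survey takes in every birth at the participating hospitals during the windows.

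**The concern.** A non-response rate is a fraction of the women approached. If it is 20%, then 80% respond, and the number to approach is the number needed divided by 0.8. The plan multiplies by 1.2 instead, which falls short at any non-response rate above zero. The 470 and the 20% are therefore incompatible with the 564 placed beside them.

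This matters because 564 is the benchmark for whether the survey windows are long enough, and it applies separately to each country in each phase. A country expected to yield between 564 and 587 births would pass that check and still fall short of 470 respondents at the plan's own non-response rate. Satisfaction is the only survey outcome for which the article makes a power statement.

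**Working it through.** **Inputs, all from the Sample size section:** difference 0.3 SD; two-sided alpha 0.05 (z = 1.96); power 90% (z = 1.2816); equal phases; design effect 2; non-response 20%; stated figures 470 and 564.

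**1. Reproduce 470.** For two means with SD 1, n per phase = 2 x (1.96 + 1.2816)² / 0.3² = 233.5. With the design effect, 2 x 233.5 = 467. Rounding 233.5 up to 234 first gives 468, and the t-test version gives 469. The stated 470 is right, and power at 470 is 90.2%.

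**2. Reproduce 564.** 470 x 1.20 = 564 exactly.

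**3. Inflation for 20% non-response.** 470 / (1 - 0.20) = 587.5, so 588. The difference is 588 - 564 = 24 women, and 24/588 = 4%.

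**4. What 564 delivers at 20% non-response.**
- Respondents: 564 x 0.8 = 451, which is 19 fewer than 470.
- Effective number per phase: 451/2 = 225.5.
- Power: Phi(0.3 / sqrt(2/225.5) - 1.96) = Phi(1.226) = 0.890. The t-test version gives 0.889.
- Difference detectable with 90% power: (1.96 + 1.2816) x sqrt(2/225.5) = 0.305 SD.

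**5. Non-response that 564 tolerates.** 1 - 470/564 = 16.7%.

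**6. Does the target bind?** 3980/4 = 995 births per country on average. At 20% non-response that is 796 respondents, and with the design effect held at 2 the power is about 98.8%. The design effect would rise with more women per hospital. Assuming eight equal hospitals, 470/8 = 58.75 women each, so a design effect of 2 implies an intracluster correlation of 1/57.75 = 0.017. At 796/8 = 99.5 women per hospital the design effect becomes 1 + 98.5 x 0.0173 = 2.7, and power is about 95%.

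The average cannot stand for every country. In Table 4, the row "Range of annual births" gives 2800 to 42,000 for Vietnam. One hospital at the top and seven at the bottom make 42,000 + 7 x 2800 = 61,600 a year, or at least about 1185 births in one week if births are spread evenly over the year. The other three countries then average at most (3980 - 1185)/3 = 932. The article does not show where each of them lies relative to 588.

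**The case against.** The strongest reply is that 564 does not set enrolment. The survey takes all births in a fixed window, no quota or stop at 564 is described, and the plan's own estimate of 3980 births is well above four times either figure (4 x 588 = 2352). This stands, with one limit: it is a statement about the total, and the plan wants conclusions for each country.

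The size is also slight even if 564 were binding. Power drops from 90.2% to 89.0%. If the design effect is allowed to fall with fewer women per hospital (to about 1.96 under the eight-equal-hospitals assumption), power is about 89.6%. A round design effect of 2 and a round 20% carry more uncertainty than that. The outcome is secondary, and the interrupted time series for the primary outcome is untouched. All of this stands. None of it makes 564 the right number for 20% non-response.

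A reader might infer from Table 4 that the windows are too short in two countries. With seven hospitals at the range minimum and one at the maximum, Argentina gives (7 x 1200 + 5600) x 2/52 = 538 births in two weeks, and Thailand gives (7 x 2500 + 7500)/52 = 481 in one week. The documents do not support that inference. These are arithmetical floors, not expected yields; the range midpoints (3400 and 5000 births a year) give about 1046 and 769. Both floors also lie below 564 as well as 588, so they have nothing to do with the inflation formula.

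**Conclusion.** The stated target is wrong for the stated non-response: 588 women per phase per country are needed, not 564. At exactly 564 women and 20% non-response there would be 451 respondents and about 89.0% power, taking the design effect as 2. The error is certain but minor: 24 women (4%) per country per phase and about one point of power, for a secondary outcome.

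A reader might go further and conclude that the survey misses its 90% power. That holds only for a country whose window yields about 564 births. Because all births are covered and 3980 are expected, the survey may well exceed 588 in every country. Without a split by country, the article neither shows this nor shows that any window is inadequate.

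**What to change.** Restate the target as 588 per phase per country (470/0.8). Alternatively, keep 564 and say that it covers 16.7% non-response and gives about 89% power at 20%.

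In either case, check each country's expected births in its survey window against 588 rather than 564, using the hospitals' delivery counts. If a fixed window falls short, state the power it gives.

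The cost is one corrected figure and a check against delivery counts. Neither the design nor the analysis changes.

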## Methods: Evaluation

### Outcomes

The primary endpoint measure is the monthly CS rate in participating hospitals among women with a singleton pregnancy, with a fetus in cephalic presentation and at least 37 weeks of gestation, and with no previous CS (groups 1-4 of the Robson classification). We will use the Robson classification to monitor CS rates at the hospital level [7, 27, 28]. This system classifies women into prospective mutually exclusive and totally inclusive groups of women based on a few obstetric variables which are easily obtained and most women themselves would know. Trained data collectors will gather information about each eligible woman using existing routine health information systems (paper-based or electronic records). We will consider the monthly rate of CS before the onset of intervention (12-month period), during the implementation phase (24-month period), and after the implementation phase (24-month period) to assess the effects of the intervention.

As secondary endpoints, the following outcome measures will be assessed: assisted vaginal delivery; time of CS (before or during labor); third- or fourth-degree perineal laceration; antibiotics and uterotonics use; transfusion; admission of the mother or the newborn to intensive care unit; uterine rupture, hysterectomy, maternal or neonatal death; time of breastfeeding initiation; woman’s satisfaction with care and her birth experience; payment for medical care; indirect costs of care for childbirth (e.g., cost of transportation to hospital); and loss of earnings. A cross-sectional survey among a representative sample of postpartum women will be established at two time points: at baseline and at the end of the intervention period. All births occurring in the participating hospitals during 2 weeks in Argentina and Burkina Faso and 1 week in Thailand and Vietnam will be covered in each survey. The data collection includes a face-to-face interview with women after childbirth and before they leave the maternity ward (facility-exit interview) and the collection of information from the women’s medical records, including socioeconomic characteristics of the mother, reproductive history, antenatal and intrapartum care, time and indication of CS, if any, satisfaction with birth experience, breastfeeding practices, out-of-pocket costs, maternal and neonatal outcomes.

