### Analysis

#### Quantitative analysis

We will use different methods to evaluate the effectiveness of the QUALI-DEC intervention [13, 14]. For the primary outcome, interrupted time series analysis (ITSA) based on segmented regression will estimate the mean changes in the level (immediate change) and trend (sustained change) of monthly CS rates across all participating hospitals in relation to their baseline level and pre-existing trend. We will follow the quality criteria proposed by Ramsay et al. for our ITSA to ensure that our study is adequately reported [35]. For secondary outcomes, we will use a before and after cross-sectional design that will include medical records and women’s interviews. We will compare the outcomes between the two periods of the cross-sectional survey, adjusting for hospital and woman characteristics, to evaluate changes in satisfaction with the birth experience, breastfeeding and medical practices, and maternal/perinatal morbidity. For implementation outcomes, checklist ratings during monitoring visits will be used to compute average scores of the fidelity, dose, and reach of the intervention. Parametric tests will be used to assess changes over time for each facility and differences between study sites.

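### The 90% power claimed separately for each country rests on a many-hospitals approximation; with 8 hospitals and the plan's full design effect of 2 it is about 80-86%

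*Protocol article*

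**What the plan says.** The Sample size section of the protocol article plans "a sample of 470 women at baseline and 470 women at the end of the intervention period" and says that this "will ensure 90% statistical power to detect an effect size of 0.3 standard deviations or greater in satisfaction scores", "with a two-sided 5% significance level". On clustering it says: "The calculation accounted for the clustered nature of the data by hospitals with a design effect of 2". The target is raised to 564 per phase for 20% nonresponse. The section then assigns this size to single countries: "This sample size will be for each country and will allow to draw conclusions independently for each country and produce individual country interpretations".

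Three other places bear on the claim:
- Targeted sites and participants gives 8 hospitals per country. Its Table 4 puts annual births in the Vietnamese hospitals at 2,800 to 42,000.
- Outcomes describes the sampling: "All births occurring in the participating hospitals during 2 weeks in Argentina and Burkina Faso and 1 week in Thailand and Vietnam will be covered". The number of women from each hospital therefore follows its volume.
- Quantitative analysis describes the comparison in one sentence: "We will compare the outcomes between the two periods of the cross-sectional survey, adjusting for hospital and woman characteristics".

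The article gives no intracluster correlation (ICC), no correlation of hospital effects between the two surveys, and no allowance for few or unequal clusters.

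**The concern.** A design effect enlarges the variance of the estimate. It does not allow for that variance having to be estimated from very few hospitals. A before-after comparison within a country rests on 8 hospital changes, so the reference distribution is a t with 7 degrees of freedom, or 14 if the two sets of hospital means are treated as independent. The plan's calculation uses normal quantiles.

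A single design effect of 2 is also hard to carry over to a country where one hospital may supply half of the women.

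At stake is whether each country's conclusion on satisfaction has the promised power. A null result in one country could be read as evidence of no effect of 0.3 SD when the design had less power to detect it than stated. The primary outcome, the monthly cesarean section rate, is not affected.

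**Working it through.** **Inputs from the article.** Difference 0.3 SD; two-sided alpha 0.05; power 90%; 470 per phase; design effect (DE) 2; 564 recruited with 20% nonresponse; 8 hospitals per country; 3,980 births expected across the four countries' survey windows; Table 4 birth ranges.

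**1. Reproducing the plan.** Women per phase without clustering: 2 × (1.96 + 1.2816)² / 0.3² = 233.5, so 234. Times 2 gives 468, against the stated 470. Power with normal quantiles: SE = √(2 × 2/470) = 0.0923; 0.3/0.0923 = 3.25; Φ(3.25 − 1.96) = 90.2%. The figure is reproduced.

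**2. Same inputs, 8 hospitals.** Noncentral t with noncentrality 3.25 (470 women), or 0.3/√(4/451) = 3.19 (451 women, from 564 × 0.8):

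| Respondents per phase | 7 df (critical 2.365) | 14 df (critical 2.145) |
|---|---|---|
| 470 | 79.6% | 85.6% |
| 451 | 78.0% | 84.2% |

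For 90% power the noncentrality must be 3.80 (7 df) or 3.49 (14 df). With 470 women the detectable difference is 3.80 × 0.0923 = 0.35 SD or 3.49 × 0.0923 = 0.32 SD.

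**3. Allowing stable hospital effects to cancel (assumption).** With equal hospitals, m = 470/8 = 58.75, and DE 2 implies ICC = 1/(58.75 − 1) = 0.0173. If r is the correlation of a hospital's effect between the two surveys, DE for the change = 1 + (m − 1) × ICC − m × ICC × r. On 7 df with 470 women:

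| r | DE | Power |
|---|---|---|
| 0 | 2.00 | 79.6% |
| 0.3 | 1.70 | 85.6% |
| 0.5 | 1.49 | 89.6% |
| 0.6 | 1.39 | 91.5% |
| 0.8 | 1.19 | 94.9% |

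Reaching 90% needs DE of about 1.47 or less, that is, r of about 0.5 or more.

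**4. The largest hospital's share in Vietnam.** One week at 42,000 births a year is 42,000 × 7/365 = 805 women; at 2,800 it is 54.
- Upper bound, with the other seven at the minimum: 42,000/(42,000 + 7 × 2,800) = 68%. Weekly total: 61,600 × 7/365 = 1,181.
- Lower bound, with the other countries at the lowest births Table 4 allows but at least 564 each: 3,980 − 564 − 901 − 564 = 1,951; 805/1,951 = 41%. The 901 is Burkina Faso: (7 × 2,500 + 6,000) × 14/365.

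**5. Power in Vietnam (assumed ICC 0.0173, 80% response, 7 df).** The variance of each hospital's change is 2 × [ICC × (1 − r) + (1 − ICC)/nᵢ]. Besides the largest hospital, the other seven are taken as equal. The two cases are 1,951 × 0.8 = 1,561 women (share 41%) and 1,181 × 0.8 = 945 women (share 68%).

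| r | Women weighted equally, share 41% / 68% | Efficiently weighted, 41% / 68% |
|---|---|---|
| 0 | 78% / 47% | 91% / 78% |
| 0.5 | 95% / 72% | 99% / 90% |
| 0.8 | over 99% / 94% | over 99% / 97% |

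With women weighted equally and r = 0, the design effect is 6.9 to 8.8 rather than 2. With hospitals this unequal, 7 df is itself an approximation.

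**The case against.** The strongest reply is that step 2 is a pessimistic corner. It takes 7 df from pairing the hospitals but keeps the full design effect, as though pairing cancelled nothing. The same hospitals are surveyed twice and the comparison adjusts for hospital, so stable differences do cancel, and moderate correlation restores 90%. The survey also covers all births. Subtracting the Vietnamese bounds from 3,980 leaves the other three countries an average of (3,980 − 1,951)/3 = 676 to (3,980 − 1,181)/3 = 933 births, or about 541 to 746 respondents. On 7 df at ICC 0.0173, 541 respondents with correlation 0.5 give 92%.

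This stands, and it is why the shortfall must be stated conditionally. It does not rescue the claim as written: the article applies the design effect in full and states no correlation. More respondents alone do not suffice on 7 df: at zero correlation, 541 give 82% and 746 give 87% (88% and 92% on 14 df).

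Three stronger readings are tempting, and the article does not support them:
- **That the planned test has inflated type I error because it omits hospital-by-period variation.** The one-sentence analysis description fixes neither the error structure nor the degrees of freedom, and a statistical analysis plan may supply both.
- **That Vietnam's power is simply low.** The ICC and the correlation are not in the article, and the ICC used here is backed out of DE 2 by assuming equal hospitals. The result runs from 47% to over 99%.
- **That women from the largest hospital should count for less.** Outcomes aims at a representative sample of postpartum women, for which weighting by births is legitimate. Down-weighting would change what is estimated.

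**Conclusion.** The point holds in a limited form. Ninety per cent power in each country is not delivered by the stated inputs once 8 hospitals are treated as 8. With the full design effect of 2, power is 80-86% for 470 respondents and 78-84% for 451, and 90% power applies to a difference of about 0.32-0.35 SD. On 7 df, 90% is recovered only if hospital effects correlate at about 0.5 or more between surveys, or if clearly more than 470 women respond and some correlation is present.

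That one Vietnamese hospital supplies 41-68% of the survey births follows from the article's own figures, so a design effect of 2 cannot be assumed there. The size of the loss in Vietnam is a range that depends on assumptions. A reader might infer that country power is about 80% as a fact, but that figure is the low end for equal hospitals at the planned sample and without correlation. The consequence is confined to a secondary outcome and its country-level interpretation.

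**What to change.** Restate the per-country power as about 80-86% for 0.3 SD, or 90% for about 0.32-0.35 SD, under the full design effect. State the assumed ICC, the assumed between-period correlation of hospital effects, the degrees of freedom and the unequal hospital sizes. If 90% is to be kept, give the correlation and number of respondents that support it.

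Base country-level tests on hospital-level variation in change. This can be a mixed model with a hospital-by-period random effect and small-sample degrees of freedom, or an analysis of the 8 hospital changes. Add a sensitivity analysis showing how far Vietnam's result depends on its largest hospital.

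The cost is a less favourable stated power and wider country intervals. No extra women or hospitals are needed.

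### The 95% CI bounds for the survey's secondary outcomes omit the design effect of 2 that the same paragraph applies to the survey, so they are too narrow

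*Protocol article*

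**What the plan says.** The Sample size section first sizes the postpartum survey on the satisfaction score: 470 women per phase and per country, 90% power, 0.3 standard deviations, two-sided 5%. Of that calculation it says: "The calculation accounted for the clustered nature of the data by hospitals with a design effect of 2". It then adds: "Allowing for a 20% nonresponse rate, we aim to recruit 564 women in each phase".

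The paragraph next turns to the pooled survey: "We estimated that 3980 births will occur during this data collection period in all participating hospitals of the four countries". From this it concludes: "This overall sample size for the cross-sectional survey will ensure accurate measurements of other secondary outcomes". Three bounds support that conclusion:

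- "Estimations of outcomes at each time point will fluctuate within a 95% confidence interval with the following bounds: 10% rate ± 1" point
- "20% rate ± 1.3% (example: second-degree perineal trauma")
- "40% rate ± 1.5%; (examples: overall CS rate, breastfeeding within 1 h of birth")

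No clustering or nonresponse allowance is mentioned for these bounds. The Outcomes section confirms that the survey is the same one, taking in every birth in the participating hospitals over one or two weeks: "All births occurring in the participating hospitals during 2 weeks in Argentina and Burkina Faso and 1 week in Thailand and Vietnam". It collects both interviews and medical-record data.

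**The concern.** The paragraph treats one survey in two ways. For satisfaction, women in the same hospital count as correlated and the sample is doubled. For morbidity, cesarean section and breastfeeding, the quoted precision matches what 3,980 independent women would give, with none lost.

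The three bounds are the only figures offered for the claim that these secondary outcomes will be measured accurately. A reader who takes them at face value will expect tighter survey estimates than the plan's own assumptions allow. The bounds are also pooled, in a paragraph that promises separate conclusions for each country, and a reader could carry them over to a single country, where they do not apply.

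**Working it through.** **Inputs, all from the Sample size section unless noted.** Births n = 3,980; rates p = 10%, 20%, 40%; 95% confidence; design effect (DE) 2; nonresponse 20%; 470 respondents per country. There are 8 hospitals per country and 32 in all (Targeted sites and participants).

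**Formula.** Half-width = 1.96 × √(p(1 − p) × DE / n).

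**Step 1: reproduce the printed bounds.** With DE = 1 and n = 3,980:

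- 10%: 1.96 × √(0.09/3980) = 0.93 points (printed 1)
- 20%: 1.96 × √(0.16/3980) = 1.24 points (printed 1.3, so rounded up)
- 40%: 1.96 × √(0.24/3980) = 1.52 points (printed 1.5)

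The 10% bound is printed to a whole point and discriminates poorly on its own. The other two settle the matter. With DE = 1 and n = 3,184 they would be 1.39 and 1.70, and with DE = 2 and n = 3,980 they would be 1.76 and 2.15. With DE = 2, the printed widths would need about 6,900, 7,300 and 8,200 women.

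**Step 2: check that DE 2 really is in the satisfaction calculation.** Two means, 0.3 SD, 90% power and two-sided 5% need 234 women per phase. 234 × 2 = 468, against the stated 470. It is.

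**Step 3: apply the paragraph's own factors.** 80% response gives 0.8 × 3,980 = 3,184 women.

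| Basis | 10% | 20% | 40% | Ratio to DE 1 on 3,980 |
|---|---|---|---|---|
| Printed | 1 | 1.3 | 1.5 | – |
| DE 1, n = 3,980 | 0.93 | 1.24 | 1.52 | 1 |
| DE 2, n = 3,980 | 1.32 | 1.76 | 2.15 | √2 = 1.41 |
| DE 2, n = 3,184 | 1.47 | 1.96 | 2.41 | √(2/0.8) = 1.58 |

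**Step 4: sensitivity to the design effect.** DE = 1 + (m − 1) × ICC, with m women per hospital. Assuming an even spread over hospitals, the per-country calculation has m = 470/8 = 58.75, so DE 2 implies ICC = 1/57.75 = 0.017. In the pooled survey m = 3980/32 = 124.4. If the same ICC held, DE = 1 + 123.4 × 0.0173 = 3.1, and the bounds on 3,980 births would be about ±1.7, ±2.2 and ±2.7.

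**Step 5: country level, DE 2.**

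- At the required 470 respondents: ±3.8, ±5.1 and ±6.3.
- At 3980/4 × 0.8 = 796 respondents (even split over countries and 80% response assumed): about ±2.9, ±3.9 and ±4.8.

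**The case against.** **The hospitals could be fixed strata.** They were chosen purposively and every birth in the window is covered, so describing rates in these 32 hospitals arguably needs no inflation for clustering. That is a legitimate view, but the paragraph does not take it: it inflates for these same hospitals when it sizes the survey. Adjusting the before-after comparison for hospital (Quantitative analysis) does not help either, because the bounds are stated for estimates at each time point.

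**The design effect is borrowed.** This stands. The value of 2 belongs to the satisfaction score, and no ICC is given for the binary outcomes. It makes the exact size uncertain but does not justify a factor of 1.

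**Nonresponse may not apply to every outcome.** This also stands. Outcomes such as mode of birth or perineal trauma may come from records, and the article does not say whether a woman who is not interviewed also loses her record data. The wider set of bounds is therefore for interview outcomes only. The plan's own convention (470 × 1.2 = 564) would give 3980/1.2 = 3,317 women and ±1.44, ±1.93 and ±2.36, a small difference.

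**Stronger readings that the article does not support.** A reader might infer that before-after changes of 2 to 3 points look detectable on the printed basis and are lost once it is corrected. That is not generally true. For two independent surveys the half-width of a difference is √2 times the single-survey value: 1.3, 1.8 and 2.2 points under simple random sampling, and 2.1, 2.8 and 3.4 with DE 2 and 80% response. A 2-point change at 40% is unresolved on either basis, and a 3-point change at 10% or 20% is resolved on both. The printed bounds also concern single time points, and hospital adjustment may remove stable between-hospital variation from a change. A reader might also derive an ICC for cesarean section from the range of hospital rates in Table 4. That would rest on a range-to-SD conversion and would count the spread among purposively chosen hospitals as sampling error.

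**Conclusion.** The bounds are wrong on the plan's own terms. They omit the design effect of 2 that the same paragraph applies to the same hospital-clustered survey. With it, the half-widths are ±1.32, ±1.76 and ±2.15 points, 41% wider than the simple-random-sample values. Where interview nonresponse of 20% applies they are ±1.47, ±1.96 and ±2.41, 58% wider. These figures assume that the satisfaction design effect carries over to the binary outcomes. If its implied ICC carried over instead, the intervals would be wider still.

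The point is minor. It concerns one descriptive sentence about secondary outcomes. It does not show that the survey is too small, and it touches neither the interrupted time series for the primary outcome nor the derivation of 470 and 564.

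**What to change.** Restate the three bounds and name their basis: design effect 2 on 3,980 births for record-based outcomes (10% ± 1.32, 20% ± 1.76, 40% ± 2.15 points), and design effect 2 with 80% response for outcomes that need the interview (± 1.47, ± 1.96, ± 2.41). State that the design effect is carried over from the satisfaction score, and that the bounds are pooled over the four countries.

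If country bounds are added, give the number of respondents that each rests on, because the required 470 and the expected 796 or so lead to clearly different widths.

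The cost is the rewording of one sentence and a less favourable stated precision. No extra women and no change to data collection are needed.
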